#### Secondary outcomes

2.6.2

The occurrence of intolerance (termination of treatment because of treatment-related AE; time frame: from V1 to V3) and the occurrence of self-reported and pre-defined (laboratory, vital signs) treatment-related SAEs (from V1 to V3 and V1 to V5) will be assessed alone as two separate secondary outcomes. Furthermore, the symptomatic efficacy of oral Fasudil will be assessed as change of MDS-UPDRS (part I to IV from V1 to V3 and V1 to V5; part I and II from V1 to V3 and V1 to V5; part III and IV from V1 to V2, V1 to V3, and V1 to V5), the change of PDQ-8 (from V1 to V3 and V1 to V5), the change of NMSQuest (from V1 to V2, V1 to V3, and V1 to V5), the change of MoCA (from V1 to V3 and V1 to V5), the change of BDI-II (from V1 to V3 and V1 to V5), and the CGI-I/PGI-I (at V2, V3, and V5).

#### Exploratory endpoints and biomaterial collection

2.6.3

Biomaterial, consisting of blood (EDTA-blood, plasma, serum, and peripheral blood mononuclear cells), tear fluid (collected with Schirmer test strips), and cerebrospinal fluid (CSF), will be collected at different timepoints throughout the study (Table 2). Pharmacokinetics of oral Fasudil and its active metabolite Hydroxyfasudil in patients with PD will be established by measurements in plasma (V1, V3, V5) and CSF (V3). ROCK activity will be quantified in the plasma at three timepoints, once before treatment (V1), once during treatment (V3), and once at the end of the wash-out period (V5). Additionally, biological samples will be available for exploratory analyses in future biomarker studies. Except for safety assessments, participation in the biomaterial collection is not a mandatory part of the ROCK-PD trial. All biomaterial samples not deemed for immediate analysis will be transferred and stored at the biobank of the Department of Neurology, School of Medicine, Technical University of Munich, Munich, Germany.

### Safety

2.7

The clinical trial will be monitored by an independent Safety Monitoring Board (SMB). The SMB will conduct regular safety reviews throughout the clinical trial to assess the progress of the trial. All adverse events (AE) will be collected from V1 (start of IMP intake). Each AE is to be classified by the investigator as “serious” or “non-serious.” This classification of the gravity of the event determines the reporting procedures to be followed. The intensity of AE will be graded using the Common Terminology Criteria for Adverse Events of the U.S. Department of Health and Human Services. All SAE will be subject to a second assessment by a medical expert, who will be independent from the sponsor. The second assessor will monitor for a relationship between SAE and IMP and expectedness of SAE (derived from reference safety information). All serious adverse reactions (SAR) will be determined a suspected unexpected serious adverse reaction (SUSAR) and require expedited reporting according to the applicable legal framework (competent authorities, ethic committees, clinical trial sites).

### Data recording and study monitoring

2.8

The documentation of the clinical trial data in adherence with the GCP-guidelines and the trial protocol is the responsibility of the investigator at the individual trial site. All essential documents will be kept in the Investigator Site File (ISF), which will be stored at the trial site in accordance with ICH GCP. Original data (source documents) remain in hospital medical records and information in the eCRF must be traceable and consistent with the original data. Source documents are, e.g., laboratory results, measurements of clinical scales, vital sign measurements, and questionnaires. No information in source documents about the identity of the patients will be disclosed. Data collected in this clinical trial and except data for exploratory analysis must be entered in an eCRF, which has to be completed by the investigator or authorized trial personnel and signed by the investigator. This also applies for those patients who do not complete the clinical trial. Every case of premature termination must be evaluated by the investigator, reasons for the termination assessed, and documented in the eCRF. The principal investigator holds the responsibility for ensuring the accuracy, completeness, and punctuality of all data submitted to the sponsor in the eCRFs and in all mandatory reports.

After database lock, the principal investigator will receive the study site data for archiving. Data are administered and processed by data management of the Münchner Studienzentrum (MSZ) with the support of a study database (eCRF). The evaluation of the data takes place by programmed validity and consistency checks.

Monitoring activities are performed to ensure that the clinical trial is conducted in accordance with the trial protocol, the principles of GCP, and local legislation. A monitoring plan will be applied, describing the scope of the monitoring activities in detail. A monitoring visit report is prepared for each visit describing the progress of the clinical trial and all identified problems. If a pandemic situation will not allow on-site monitoring, then remote monitoring or monitoring by phone is possible if data protection aspects are considered.

### Sample size calculation

2.9

Expected probability for occurrence of the composite endpoint in the placebo arm is 5% at end of clinical trial. The two Fasudil arms are expected to reach about 12% each (according to the summary of product characteristics [SmPC] of Eril). A non-inferiority margin of 25% for the difference between Fasudil and placebo will be used based on data from previously published trials showing rates of discontinuation and severe adverse events of up to ~25% in patients treated with drugs that are in current clinical use for PD. For example, increased mortality was observed under selegiline/levodopa treatment (Lees, 1995), while side-effects (e.g., somnolence, dizziness, nausea) resulted in discontinuation in pramipexole-treated patients (Nissen et al., 2012; Schapira et al., 2013; Wang et al., 2017). Both drugs are in current use for PD. We thus consider a non-inferiority margin of ~25% as clinically and ethically acceptable for a drug that can have potentially disease-modifying properties and symptomatic effects. The two Fasudil arms will be tested against placebo in a hierarchical order, starting with the lower dose. This sequential procedure does not necessitate adjustment of the alpha level for multiple testing (Committee for Proprietary Medicinal Products (CPMP), 2002). According to the procedure no confirmatory claim can be based on the second test if the first test did not reach statistical significance. The significance levels are therefore each set to 10%, resulting to an overall type-I error of 10%. This error level was chosen in concordance with the recommendation of the European Medicines Agency (Committee for Medicinal Products for Human Use (CHMP), 2005). Given the aforementioned expected event rates, the non-inferiority margin and the alpha level of 10%, the sample size in each group needs to be 22 for a one-sided two-group test of proportions to reach a power of 80% to reject the null hypothesis that Fasudil is inferior to placebo in terms of its composite primary endpoint (calculated by nQuery Advisor V7.0, Statcon GmbH, Witzenhausen, Germany). A total of 3 × 25 = 75 patients are included in order to account for possible dropouts (for reasons other than intolerance; 12% drop-out).

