#### Primary endpoint analysis

2.10.2

The overall confirmatory significance level is set at 10%. The two primary hypotheses are that each Fasudil arm is non-inferior to the placebo arm referring to the composite primary endpoint. The two hypotheses are tested in a sequential order, first comparing arm B (=lower dose) against placebo and second comparing arm A (=higher dose) against placebo. A confirmatory claim can only be based on the second test if the first test did reach statistical significance. For each of the primary hypothesis tests, an exact one-sided 90% confidence interval (CI) of the differences (defined as placebo minus Fasudil) in the primary outcome will be computed to test non-inferiority. Statistical significance of non-inferiority is reached if the lower limit of the respective 90% CI is above the non-inferiority margin of −25%. Patients who leave the clinical trial prematurely due to reasons other than drug intolerance and treatment-related SAEs (e.g., refusal to come to follow-up visits, relocation to another city), will be excluded from the primary endpoint analysis.

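### The 80% power at 22 per arm matches a large-sample test; the exact interval fixed for the primary analysis gives at best about 68% to 73% for the low dose at 22 to 25 evaluable per arm

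*Protocol article*

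**What the plan says.** Section 2.9 (Sample size calculation) sets the inputs. The placebo rate is 5% at the end of the trial. For the active treatment, "The two Fasudil arms are expected to reach about 12% each". On the margin, the section states: "A non-inferiority margin of 25% for the difference between Fasudil and placebo will be used". On alpha it says "The significance levels are therefore each set to 10%, resulting to an overall type-I error of 10" per cent. From these it concludes that "the sample size in each group needs to be 22 for a one-sided two-group test of proportions to reach a power of 80" per cent, and adds a 12% dropout allowance to reach 25 per arm, 75 in total. It does not name the formula, and it does not say that the test used for sizing is exact.

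Section 2.10.2 (Primary endpoint analysis) fixes the analysis: "an exact one-sided 90% confidence interval (CI) of the differences (defined as placebo minus Fasudil) in the primary outcome will be computed to test non-inferiority". Non-inferiority holds if the lower limit lies above −25%. Patients who leave for reasons other than intolerance or treatment-related SAEs are excluded, so about 22 per arm are analysed if dropout is as assumed. The lower dose is tested first, and "A confirmatory claim can only be based on the second test if the first test did reach statistical significance". The type of exact interval is not named.

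**The concern.** The two sections describe different procedures. At 22 per arm the design expects 22 × 0.05 = 1.1 placebo events and 22 × 0.12 = 2.6 Fasudil events. With counts this small a normal approximation is a poor guide to an exact procedure, whose rejection region can change only in whole patients and must keep its size at or below 10% for every possible placebo rate. If the exact interval has clearly less power than 80%, the plan understates the risk of failing to show non-inferiority when the drug behaves as assumed. The choice of exact interval could then also decide the result in data close to the design assumptions.

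**Working it through.** **Inputs (section 2.9):** placebo rate 0.05; Fasudil rate 0.12; margin 0.25; one-sided alpha 0.10 (z = 1.2816); power 0.80 (z = 0.8416). The distance from the assumed difference to the margin is 0.25 − 0.07 = 0.18.

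**Step 1: the stated figure.**
- Unpooled variance: (1.2816 + 0.8416)² × (0.05 × 0.95 + 0.12 × 0.88) / 0.18² = 4.508 × 0.1531 / 0.0324 = 21.3, so 22.
- Pooled variance (mean rate 0.085): 4.508 × 2 × 0.085 × 0.915 / 0.0324 = 21.6, so 22.
- Approximate power at 22 (unpooled): 0.18 / √(0.1531/22) − 1.2816 = 0.876, which is 81.0%.
- Dropout: 22 / 0.88 = 25.

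The stated 22 and 25 are therefore correct for a large-sample test.

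**Step 2: power of an exact interval at 22 per arm.** The exact unconditional one-sided 10% test of a 25-point difference was inverted to the one-sided 90% interval, with size maximised over the unknown placebo rate. All binomial outcomes were enumerated. With score ordering, non-inferiority is declared up to these Fasudil counts:

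| Placebo events | Probability at 5% | Largest passing Fasudil count | P(Fasudil count ≤ this) at 12% | Product |
|---|---|---|---|---|
| 0 | 0.3235 | 2 | 0.4983 | 0.161 |
| 1 | 0.3746 | 3 | 0.7328 | 0.275 |
| 2 | 0.2070 | 4 | 0.8847 | 0.183 |
| 3 | 0.0726 | 4 | 0.8847 | 0.064 |
| 4 | 0.0182 | 5 | 0.9593 | 0.017 |

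These rows sum to 0.701. Placebo counts of 5 or more add 0.004, giving 70.5%. The actual size is 9.5%.

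The region has almost no room to grow. Adding the next outcome raises the size above 10% for each placebo count from 0 to 5: to 16.2% for 0 placebo and 3 Fasudil events, and to 12.6% for 1 and 4. The loss is therefore not caused by a clumsy exact method.

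**Step 3: other orderings and other evaluable numbers.** Low-dose power:

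| Exact interval | 22 per arm | 23 | 24 | 25 |
|---|---|---|---|---|
| Score | 70.5% | 69.3% | 67.6% | 72.6% |
| Wald ordering | 67.3% | – | – | 72.5% |
| Raw difference | 28.6% | 48.6% | 47.2% | 45.7% |

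With the raw difference at 22 per arm, the rule can only be that the Fasudil count does not exceed the placebo count (size 6.1%). Allowing one event more would give a size of 10.7%. A result of 1 placebo and 3 Fasudil events out of 22 each, close to the design assumption, therefore passes with the score interval and fails with the raw-difference interval.

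Score-based power first reaches 80% at 31 per arm (83.0%).

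**Step 4: the fixed sequence.** Both doses share one placebo arm. Squaring the conditional pass probability in the Step 2 table before averaging gives the probability that both doses pass. With the score interval and 12% in both Fasudil arms, this is 52.1% at 22 per arm, 50.9% at 23, 48.8% at 24 and 54.0% at 25.

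**The case against.** Several counter-arguments have weight.

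- **The sample size is not miscalculated.** This is true. Both the unpooled and the pooled formula give 22. The article does not name its formula, so the large-sample origin is an inference from this agreement. What fails is the transfer of the 80% to a different analysis.
- **The article does not name the exact interval, and the SAP or full protocol may do so.** This is fair, and not naming it is no error in itself. The 70% is conditional on score ordering, and nothing in the document says that the raw-difference version will be used. But score ordering was the most favourable version tried, and no version tried reaches 80% at 22 to 25 per arm. The mismatch does not depend on what the SAP says.
- **The Fasudil rate is only approximate.** With 5% on placebo and 10% on Fasudil, the score interval has 79.5% power at 22 and 82.2% at 25; with 15% on Fasudil it has 56% at 22. The power claim in 2.9 is tied to 12%, so it must be judged at 12%.
- **A positive result stays valid.** This stands. The exact interval keeps type I error at or below 10%. The large-sample Wald interval has true power 78.6% at 22, but its type I error reaches 16.2%. That is no defect of this trial, which does not plan to use it; it is only a reason not to restore the 80% by dropping the exact method.

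A reader might also infer that the roughly 52% chance of claiming both doses refutes the stated 80%. It does not. Section 2.9 gives 80% for one two-group comparison and openly makes the high-dose claim conditional on the low dose. Nor does the document say that a failed test will be taken as evidence of harm, so that consequence should not be asserted.

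**Conclusion.** The power statement in 2.9 is wrong for the analysis in 2.10.2. Under the plan's own assumptions, the best exact interval tried has about 68% to 73% power for the low dose over 22 to 25 evaluable patients per arm, so the type II error is about 27% to 32% where 20% is stated. Even with no dropouts, 80% is not reached. Power is saw-toothed in this range, lower at 23 and 24 than at 22, so a range describes it better than a single rising figure.

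The conclusion rests on rates of exactly 5% and 12%, equal arms, one-sided alpha of 10% and an unconditional exact interval with score ordering. Other orderings give the same or less power. The 49% to 54% for both doses further assumes 12% in each Fasudil arm and is a consequence that the article leaves unstated. The validity of a positive finding is not affected.

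**What to change.** Keep 75 patients and keep the exact analysis.

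1. In 2.9, replace the 80% by the power of the planned exact interval: about 70% for the low dose at 22 evaluable per arm, range 68% to 73% over 22 to 25. The 80% may remain only if labelled as a large-sample approximation.
2. In 2.10.2, name the exact unconditional interval based on the score statistic (Chan-Zhang), before unblinding. The raw-difference version would lose most of the power.
3. In 2.9, add that the probability of claiming both doses under the fixed sequence is about 49% to 54% if both Fasudil rates are 12%.

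The cost is a few sentences and a less favourable stated power. No patients are added and the design does not change.

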### Statistical analysis

2.10

#### Analysis set

2.10.1

The primary analysis will be performed on the safety analysis set, consisting of all patients randomized into the clinical trial and who took at least one dose of study medication, allocated to the treatment actually received (analysis “as treated,” not “as randomized”), as the primary analysis concentrates on safety and/or tolerability. Patients with missing primary endpoint assessments will be excluded from this analysis. The full analysis set (FAS) consists of all patients randomized into the clinical trial who took at least one dose of study medication and will be analyzed according to the intention-to-treat (ITT) principle, i.e., “as randomized.” If all patients receive the treatment for which they were randomized, the safety analysis set and the FAS are identical. The per-protocol set (PPS) consists of all patients in the FAS who have no major protocol deviations. Patients with protocol deviations will be identified in a blinded manner prior to database lock. Safety and/or tolerability endpoints will be analyzed on the safety set. Analysis of the primary endpoint will additionally be performed on the PPS, as it is more conservative in the non-inferiority setting. All other endpoints will be analyzed on the FAS and PPS. Missing values will not be imputed in this clinical trial.

#### Primary endpoint analysis

2.10.2

The overall confirmatory significance level is set at 10%. The two primary hypotheses are that each Fasudil arm is non-inferior to the placebo arm referring to the composite primary endpoint. The two hypotheses are tested in a sequential order, first comparing arm B (=lower dose) against placebo and second comparing arm A (=higher dose) against placebo. A confirmatory claim can only be based on the second test if the first test did reach statistical significance. For each of the primary hypothesis tests, an exact one-sided 90% confidence interval (CI) of the differences (defined as placebo minus Fasudil) in the primary outcome will be computed to test non-inferiority. Statistical significance of non-inferiority is reached if the lower limit of the respective 90% CI is above the non-inferiority margin of −25%. Patients who leave the clinical trial prematurely due to reasons other than drug intolerance and treatment-related SAEs (e.g., refusal to come to follow-up visits, relocation to another city), will be excluded from the primary endpoint analysis.

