### Objectives and design

2.1

The objective of the ROCK-PD trial is to establish a safety and tolerability profile of the ROCK-inhibitor Fasudil by testing for non-inferiority against placebo, and asses symptomatic efficacy in patients with PD. It is designed as a multi-center, prospective, interventional, randomized, double-blind, placebo-controlled, parallel-group, phase IIa trial. In brief, patients with PD, who are non-fluctuating on their antiparkinsonian medication, will be recruited to receive either Fasudil in two dosages, or placebo, over a period of 22 days. Two follow-up visits (until day 50) will establish safety and symptomatic effects during wash-out (Figure 1). The SPIRIT guidelines were followed in the preparation of the trial protocol (Chan et al., 2013; Supplementary Table S1) and study results will be published in accordance with the CONSORT guidelines (Moher et al., 2010).

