#### Primary outcome

2.6.1

The composite primary endpoint consists of the occurrence of intolerance, defined as termination of treatment because of treatment-related adverse effects (AE), and/or self-reported or pre-defined (laboratory, vital signs) treatment-related serious adverse effects (SAE) from day 1 (V1) to day 22 (V3) of the treatment period.

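### The primary-analysis exclusion is triggered by leaving a 50-day trial, not by missing day 1–22 data, so as written it discards known outcomes, including observed events

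*Protocol article*

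**What the plan says.** The Primary outcome section (2.6.1) counts intolerance and treatment-related SAEs "from day 1 (V1) to day 22 (V3) of the treatment period". The intolerance component is "occurrence of intolerance, defined as termination of treatment because of treatment-related adverse effects (AE), and/or" a treatment-related SAE. It is therefore an event about stopping drug, not about leaving the trial.

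The trial continues after that window. Objectives and design (2.1) states: "Two follow-up visits (until day 50) will establish safety and symptomatic effects during wash-out". Table 2 places these visits at day 36 (V4) and day 50 (V5).

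Two sentences decide who is left out of the primary analysis:

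- Analysis set (2.10.1): the safety set is described as "consisting of all patients randomized into the clinical trial and who took at least one dose of study medication", and then "Patients with missing primary endpoint assessments will be excluded from this analysis". The same section adds: "Missing values will not be imputed in this clinical trial".
- Primary endpoint analysis (2.10.2): "Patients who leave the clinical trial prematurely due to reasons other than drug intolerance and treatment-related SAEs" are removed, with the examples and consequence "e.g., refusal to come to follow-up visits, relocation to another city), will be excluded from the primary endpoint analysis".

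**The concern.** The two exclusion sentences use different triggers. Section 2.10.1 asks whether the day 1–22 outcome is missing. Section 2.10.2 asks why a patient left a trial that runs 28 days beyond the endpoint window (50 − 22 = 28), and its first example is refusal of follow-up visits, the term section 2.1 uses for the wash-out visits. Its exception depends on the reason for leaving, not on whether an event occurred.

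Who enters the only confirmatory comparison would then depend partly on behaviour after the endpoint has closed. Some discarded patients would be event-free and some would carry a counted event. With 25 patients per arm, a single such patient can matter when the table is close to the decision boundary.

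**Working it through.** **Step 1. The two triggers applied to the same patients.**

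| Patient | Day 1–22 outcome | 2.10.1 | 2.10.2, read literally |
|---|---|---|---|
| Completes V3 event-free, refuses V4/V5 | known, no event | kept | excluded |
| Treatment-related SAE on day 5, relocates on day 15 | known, event | kept | excluded |
| Stops drug for intolerance, stays in the trial, relocates after V3 | known, event | kept | excluded |
| Leaves before V3 without an event, other reason | unknown | excluded | excluded |

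The rules agree only in the last row. In the first three, section 2.10.2 removes a known outcome.

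**Step 2. The planned size (section 2.9).** Inputs: placebo 5%, Fasudil 12%, margin 25 points, one-sided alpha 10%, power 80%. With the unpooled normal formula,

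n = (1.2816 + 0.8416)² × (0.12×0.88 + 0.05×0.95) / (0.25 − 0.07)² = 4.508 × 0.1531 / 0.0324 = 21.3, rounded up to 22.

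22 / (1 − 0.12) = 25 per arm, 75 in total. The plan's figures reproduce. The allowance for losses is 3 per arm.

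**Step 3. What one excluded patient does.** The protocol specifies an exact one-sided 90% interval without naming the method. I used an exact unconditional test at the 25-point margin, with the score statistic (restricted maximum-likelihood variance) as ordering and the p-value maximised over the nuisance rate. Non-inferiority is shown if p is at most 0.10.

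| All known outcomes kept (Fasudil vs placebo) | p | After one exclusion | p |
|---|---|---|---|
| 4/25 vs 1/25 | 0.103, not shown | one Fasudil event lost: 3/24 vs 1/25 | 0.048, shown |
| 5/25 vs 2/25 | 0.118, not shown | one Fasudil event lost: 4/24 vs 2/25 | 0.068, shown |
| 3/25 vs 0/25 | 0.096, shown | one event-free Fasudil patient lost: 3/24 vs 0/25 | 0.115, not shown |

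The tables that flip depend on the ordering. With raw-difference ordering, the first pair is 0.210 and 0.114 (no flip), the third is 0.210 and 0.181 (no flip), and 4/25 vs 2/25 (0.137, not shown) becomes 3/24 vs 2/25 (0.068, shown).

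**Step 4. Type I error at true rates of 30% vs 5% (25 per arm, score ordering, exclusion shares assumed).** With no exclusions it is about 7%. With 12% of all patients excluded regardless of outcome it is about 8%. With 12% of Fasudil event patients alone excluded it is about 12%. With 24% or 36% of Fasudil event patients excluded, against 12% of everyone else, it is about 12% or 19%. Clear inflation needs Fasudil events to be lost more often than other outcomes.

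**Step 5. Power.** Normal-approximation power is Φ(0.18/√(0.1531/n) − 1.2816), which is 84.6% at n = 25 and 81.0% at n = 22. If all three allowed losses per arm were patients with known outcomes, about 3.6 points of power would be given away.

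**Step 6. A separate scenario: intolerance recorded as another reason.** If a share f of Fasudil events is lost this way and nobody else is excluded, the observed Fasudil rate at the margin is 0.30(1 − f)/(1 − 0.30f). For f = 1/4, 1/3 and 1/2 this is 24.3%, 22.2% and 17.6%. With 22 per arm, the chance of a false non-inferiority claim rises from 8.6% to 20%, 26% and 44%. This measures miscoding of the reason for leaving, not the window problem.

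**The case against.** The strongest reply is that section 2.10.2 is only loosely worded. The sample size section budgets 12% dropouts for reasons other than intolerance, and section 2.10.1 already excludes missing endpoints, so the authors may have meant only event-free patients who leave before V3. That is plausible, but the sentence does not say so, its first example points to visits after the window, and under that reading it would add nothing to section 2.10.1. The ambiguity stands.

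Three stronger readings are tempting, and the document does not support them.

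- A reader might infer that the rule contradicts a promise to analyse every treated patient. It does not: section 2.10.1 itself excludes missing endpoints. The conflict is between two exclusion triggers.
- A reader might fault the lack of a sensitivity analysis for early leavers. This is a condensed article and the analysis plan is not shown, so that absence is no finding. The stated per-protocol analysis is no clear remedy, because it is drawn from a subset and the exclusion is stated for the primary endpoint analysis as such.
- A reader might take 20–44% as the size of this defect. Those figures assume that only Fasudil events are lost, through miscoding before V3, and a rule tied to the window would not remove that risk. Patients and investigators are blinded, and section 2.8 requires each premature termination to be evaluated and its reason documented. An adverse event judged unrelated is not an endpoint event either, so excluding that patient loses no defined event.

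**Conclusion.** The rule is wrong as written. It discards known day 1–22 outcomes and does not match the missing-endpoint rule in section 2.10.1.

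Its effect has no fixed direction. Losing an observed Fasudil event favours non-inferiority. Losing an event-free Fasudil completer, the case closest to the protocol's own example, raises the observed Fasudil rate and so generally works against it. The document does not support inferring that the rule systematically biases the trial towards its claim: exclusion unrelated to outcome leaves type I error near 7–8%.

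One patient decides the result only in borderline tables. The flips in Step 3 rest on the score ordering, which is my assumption, and all exclusion shares are assumed because the document gives none. The sample size is not at fault. This should be fixed, ideally before unblinding, but it does not undermine the design.

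**What to change.** Tie the rule in section 2.10.2 to V1–V3 and align it with section 2.10.1:

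1. Any treated patient with intolerance or a treatment-related SAE up to V3 counts as an event, whatever the later reason for leaving.
2. Any patient who reaches V3 event-free counts as a non-event, whatever happens at V4 or V5.
3. Only patients who leave before V3 without an event are excluded as missing.

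Optionally, add a sensitivity analysis that counts Fasudil early leavers as events and placebo early leavers as non-events. This addresses the separate miscoding risk in Step 6.

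The cost is one or two sentences, plus one table if the optional analysis is added. The planned number of patients does not change. The results may look slightly less favourable.
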